##### Single items

*Socio-demographic data.* The data collected includes information about gender, age, marital status, the highest educational level attained, the number of years worked under the current leader, organizational tenure and hours of direct contact with leader per week.

*Change-related data. P*articipants will be asked to rate the statement “I have noticed a change in my leader’s behavior after the training.” This item will be assessed on a 5-point Likert scale ranging from 1 “do not agree” to 5 “fully agree”; respectively there will be another option “My leader will take part in the training in 2022”. This item will only be used at T1 and T2.”.

At the end of the survey participants will have to answer two additional questions. At first, they have to indicate their seriousness during participation [67]. Therefore, we will directly ask participants if questions were answered in a serious manner (“Please indicate whether you have been actively involved in the survey, so that we can use your answers for our scientific analysis, or whether you were just clicking through to gain a first impression?”). Second, employees can decide, whether their answers can be used for a de-identified employee summary report, which will be provided for the leaders after the completion of T2.

##### Questionnaires

*Short questionnaire for work analysis* (ger.: Kurzfragebogen zur Arbeitsanalyse, KFZA, [68]). Working conditions will be assessed by the KFZA, which consists of eleven scales derived from 26 items. These scales comprise Decision latitude, Variety of work, Task identity, Social support, Teamwork, Workload (qualitative), Workload (quantitative), Interruption of work, Environmental stress, Information and codetermination, Company benefits. Sample items are: “How much influence do you have on what work is assigned to you?” and “I am often under time pressure”. All items are measured on a 5-point Likert scale ranging from 1 “does not apply at all” to 5 “is completely true”. The internal consistency of the scales is set between .40 and .76 (Cronbach’s α); in studies with larger samples Cronbach’s α ranged from .63 to .80 [69].

*Cognitive and emotional irritation scale* (IS [70]). The IS measures perceived cognitive and emotional strain. Irritation refers to a psychological state of impairment due to the experience of goal-discrepancy. The IS consist of 8 items that have to be answered on a 7-point Likert scale resulting in two first-order factors: First, Rumination (e.g., “Even when I am on vacation, I sometimes have to think about problems at work”) invokes increased efforts in order to achieve goals, whereas the second factor Irritability (e.g., “I get angry easily”) reflects a tendency to lose the incentive to pursue a certain goal. Internal consistency scores range from .85 to .97 for both subscales.

*Subjective psychological well-being* (WHO-5, Bech et al., 2003). Employees’ well-being will be measured using the five-item World Health Organization Well-Being Index (WHO-5) representing the most widely used questionnaire for measuring this construct [71]. Items are assessed on a 6-point Likert scale, ranging from 0 “at no time” to 5 “all of the time” concerning the last 2 weeks (e.g., “… I have felt calm and relaxed”). The raw score is multiplied by 4 resulting in a final score ranging from 0 to 100 (representing the best possible well-being). The WHO-5 is suitable for depression screening. The split-half reliability (Guttman’s coefficient) is r_tt_ = .87 (Brähler et al., 2007).

*Effort Reward Imbalance* (ERI, [53]) and *Relationship between employees and their managers* (LMX-7, Schyns & Paul, 2014). Both questionnaires are already described in section 2.3.1.

*Serial qualitative interviews in the intervention group*. We will conduct serial qualitative interviews at T_0_ and T_2_ as interviewing participants on multiple occasions is useful in understanding longitudinal change, thus variation in behaviours or circumstances over time [72]. Particularly, semi-structured interviews with employees will be used in order to understand the delivery and impact of indirect outcomes on employees following their leaders‘participation in the intervention. Thus, employees will be asked to describe the leadership behaviour, the leader’s stress level, leadership styles, working conditions and self-perceived health in a narrative style. Following a qualitative content analysis [73] the preliminary category system developed at T_0_ will be revisited at T_2_ in order to identify potential changes.

### Timeline

The total trial duration is 12 months for the intervention group, and 18 months for the control group. Baseline data of all leaders and employees is going to be collected in the beginning (spring 2021). The intervention group participates in the stress management training in the weeks thereafter (duration: 1.5 days) followed by two booster sessions 3 and 6 months later, each lasting for 180 min. All participants are going to be measured again after 6 and 12 months. Afterwards, participants of the waiting control group are going to participate in the training, followed by the two booster sessions 3 and 6 month thereafter.

### Assignment of interventions

Each single participant will randomly be allocated to the intervention or waiting control group. A study staff member uses computer-generated random numbers for the allocation of the participants. It is not possible to blind participants about their group affiliation, due to the different intervention times.

### Data collection, management, and analysis

*Data collection.* Leaders’ sociodemographic and work-related data will be assessed at baseline before the intervention. The self-report measures of health-related indices, perceived stress (PSRS-23 [52]), work satisfaction (ERI [53]), symptoms of depression and anxiety (HADS-D [74]) and well-being (WHO-5 [75]) will be assessed at three different points of time: at baseline, at a 6-month-follow-up post-intervention and a 1-year-follow-up. The questionnaires can be filled in at home or during the clinic visits, where the physiological data will be recorded across the three time points. All questionnaire data will be assessed online via the encrypted German Unipark servers. Physiological measures, i.e. hair cortisol, saliva samples for alpha-amylase activity and blood pressure will be collected by a trained study nurse on site. To assess the 24-h-heart rate variability, participants will wear a belt for 24 h after their appointment at the clinic. Employees will receive online questionnaires that can be filled in during work in order to rate their individual stress levels and their perceived interaction with their leaders. Data will be transmitted electronically across encrypted German servers provided by the online assessment tool Unipark.

#### Data management

All data will be stored pseudonymously. All identifying information of participants will be removed from the datasets. Data will be stored locally on the clinic networks that underlie a strict security protocol to store sensitive clinical data. If data will need to be transferred electronically, it will be password encrypted. Documents with identifying information, such as signed consent to participation will be stored securely and separately from the study data. Only project staff members will have access to the data collected. The staff members are subject to the obligation of secrecy.

#### Statistical methods

Data will be analysed using the statistic software IBM SPSS Statistics 27. Descriptive analyses will be conducted after the baseline. A multivariate analysis of variance (MANOVA) with all relevant outcome parameters as specified above will be calculated in order to test the effects of the intervention on different dependent variables. Potential covariates will be included in the analysis. Therefore, if relevant covariates occur, a MANCOVA will be performed instead of the MANOVA. A covariate will be identified as such, if a demographic variable will correlate with the outcome variable or if there is a significant difference between the intervention group and the waitlist control group across this variable.

To evaluate the effects of the stress management intervention more specifically, changes in outcome variables will be analysed by two-factorial ANOVA with repeated measures and group (intervention vs. waiting control group) as a between-person effect. The core hypothesis is that perceived stress and physiological stress parameters of leaders will significantly decrease from baseline to follow-up measurements for participants in the intervention group. Thus, we will test the interaction effect of time x group for the different outcome variables. Where necessary, Bonferroni correction will be applied to avoid inflation of the type one error by multiple comparisons.

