### Trial design

The study is designed as a randomized 2 × 3-mixed design (factor 1 (group): intervention or waiting control group; factor 2 (point in time): baseline, 6 months and 12 months later; see Fig. 1). All participating leaders are going to be randomly assigned to one group. Baseline measures of participants of the intervention group are going to be collected about 2 weeks before their group intervention takes place. Baseline measures of participants of the waiting control group are going to be collected simultaneously. The intervention group is going to take part in the stress management training, followed by two booster sessions after 3 and 6 months. Participant’s satisfaction with the intervention is planned to be assessed within 2 weeks after the intervention. After 6 and 12 months, all relevant outcome variables are planned to be measured (for more detailed information about the outcome variables, please see Section 2.3). The waiting control group will also be measured for all relevant outcome variables after 6 and 12 months, but is going to take part in the intervention only after the last measurement. Employees of the participating leaders will be measured at the same points in time: baseline, 6 and 12 months later.

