## Method

### Population and sample size

#### Leaders

The target group are leaders of small and medium-sized enterprises (SMEs). We define SMEs as enterprises with up to 500 employees [50, 51] without regarding the annual sales. Leaders of all genders aged between 18 and 65 years are allowed to participate as long as they are not about to retire within the next year. A sample size of *n* = 100 participants in the intervention group and *n* = 100 participants in the waiting control group is planned (*N* = 200 participants).

The sample size calculation was performed using G*Power3.1. Based on a 2 × 3-mixed design (factor 1 (group): intervention or waiting control group; factor 2 (point in time): baseline, 6 months and 12 months later) the required sample size for a MANOVA with measurement repetition was estimated using the following predefined parameters: mean effect size f = .25 (Ω = 0.06), α-error = .05, test strength 1-β = .80. This results in a required sample size of *n* = 158 participants (*n* = 59 per group). The calculation of the required sample size was based on the procedure proposed by Prajapati et al. (2010) to calculate the required sample sizes for all possible effects (within, between, interaction) of the present design and to use the largest calculated sample size. Due to the high effort of the outcome criteria to be collected (e.g., saliva samples, 24-h heart rate variability) a high lost-to-follow-up as well as numerous missing values can be expected. We therefore calculate with a total failure rate of 21% (lost-to-follow-up and due to missing values), resulting in a required sample size of *N* = 200 (*n* = 100 per group at T_0_).

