### Intervention

The implemented stress management training is based on the successfully conducted intervention of the MAN-GO project [48]. It is going to be adapted based on the results of a previous (and still ongoing) needs analysis concerning format and content. Depending on the results, it will most likely obtain the following modules:
Stress: effects of stress, individual stress symptoms, mentalization ability under stressWork stress models: gratification model, demand-control-model, organizational fairnessLeadership: stress-preventive, health-oriented, and relational leadership, leaders as role models, new demands on leaders based on COVID-19 and the digitalizationShort term relief: brooding strategies, attention guidingConflict management: dealing with (emotional) conflicts and catch-22 situations at the workplaceRelaxation: progressive muscle relaxation, 1-min meditationResources: sweet spot imagination, social support, 10 fingersCase work: working on cases brought in by participants, approach based on Balint groups and collegial case adviseOptional additive online modules: impact of stress on cardiovascular diseases, further stress symptoms

Trainings are going to take place in groups with 8–12 leaders and are held by two trainers. As far as possible in the context of COVID-19, they should be carried out in persona. Concerning the didactical frame, the trainings consist of a mixture of lectures, open discussions as well as single, peer, and group work. Trainings will take place in Ulm and surrounding as well as in Tuebingen and surrounding.

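### Leaders are trained in groups in one arm only, but the planned ANOVA and the sample size treat all leaders as independent; unless the training-group correlation is zero, the tests are anti-conservative and 80% power at a true 5% level is not secured

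*Protocol article*

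**What the plan says.** All statements are in the protocol article.

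- **Assignment of interventions:** "Each single participant will randomly be allocated to the intervention or waiting control group".
- **Intervention:** "Trainings are going to take place in groups with 8–12 leaders and are held by two trainers". On format, "the trainings consist of a mixture of lectures, open discussions as well as single, peer, and group work". The planned modules include case work on participants' own cases. Two booster sessions follow.
- **Trial design:** the waiting control group "is going to take part in the intervention only after the last measurement".
- **Population and sample size, Leaders:** the stated inputs are "mean effect size f = .25 (Ω = 0.06), α-error = .05, test strength 1-β = .80" for a 2 × 3 repeated-measures MANOVA. This gives 158 analysed leaders, raised to 200 for a 21% failure rate. That is the only inflation.
- **Statistical methods:** after an overall MANOVA (or MANCOVA, with demographic variables as the candidate covariates), "changes in outcome variables will be analysed by two-factorial ANOVA with repeated measures and group (intervention vs. waiting control group) as a between-person effect". The time × group interaction tests the core hypothesis. No term for training group or trainer appears, and no ICC or design effect is given.

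**The concern.** Leaders who sit in the same group share trainers, discussions, case work and, in all likelihood, boosters. Their changes from baseline can therefore be correlated. Controls have no training groups during follow-up, so any such correlation exists in one arm only. A repeated-measures ANOVA whose only between-unit error is person-to-person variation cannot separate a training effect from chance differences between about ten groups, and its error term is too small. Bonferroni correction does not address this. It corrects for the number of tests, not for a wrong standard error within each test.

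At stake is the test of the core hypothesis on leaders' stress outcomes. The error makes a claim of effect easier to reach. The sample size rests on the same independence assumption, so its alpha and power cannot both hold if the correlation is above zero.

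**Working it through.** **Inputs from the protocol article.** f = 0.25, so f² = 0.0625; alpha 0.05; power 0.80; two arms, three times; 158 analysed; 21% failure; 100 per arm enrolled; groups of 8–12. The sample-size paragraph prints 59 per group beside 158. Since 158/2 = 79, I use 79 per arm.

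**Assumptions.** The ICC of change within a training group is 0.02, 0.05 or 0.10, taken as equal for both time contrasts. There are 100/10 = 10 groups, with 79/10 = 7.9 analysed leaders per group.

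**Step 1: reproduce the stated figure.** For the multivariate time × group test, λ = N·f² = 158 × 0.0625 = 9.875, with df 2 and N − 3 = 155. Power is 80.2%. At N = 157 it is 79.9%, so 158 is the minimum. Enrolment is 158/0.79 = 200. The figure reproduces, with no slack.

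**Step 2: design effect, one arm nested.** With b = 7.9, the variance of the intervention-arm mean is multiplied by 1 + (b − 1)·ICC and that of the control mean by 1. On average, DE = 1 + (b − 1)·ICC/2.

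- ICC 0.02: 1 + 6.9 × 0.02/2 = 1.069
- ICC 0.05: 1 + 6.9 × 0.05/2 = 1.1725
- ICC 0.10: 1 + 6.9 × 0.10/2 = 1.345

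The naive standard error is 1/√DE of the true one: 0.967, 0.924 and 0.862, so about 3%, 8% and 14% too small.

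**Step 3: type I error of the planned test.** The critical value of F(2,155) is 3.054. Under the null the statistic is inflated by about DE, so the true level is about P(F > 3.054/DE). For F(2,d) this tail is (1 + 2x/d)^(−d/2).

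- ICC 0.02: x = 2.857, giving 6.0%
- ICC 0.05: x = 2.605, giving 7.7%
- ICC 0.10: x = 2.271, giving 10.7%

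Simulations of the planned multivariate test with 10 groups of 7–8 agree: 5.9–6.4%, 7.6–8.2% and 10.7–11.1% across runs, and about 5% at ICC 0. With other layouts (such as 8 groups of 10) or another pattern of the group effect over time, the range is about 6%, 7–9% and 9–13%.

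**Step 4: power of a valid test at 158 analysed.** λ = 9.875/DE. The small-group df follow Satterthwaite. With V = 1 + (b − 1)·ICC, df = (V + 1)²/(V²/9 + 1/78), less one for the second time contrast.

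| ICC | λ | Power, df 155 | Small-group df | Power, small-group df |
|---|---|---|---|---|
| 0.02 | 9.24 | 77.4% | 28 | 73% |
| 0.05 | 8.42 | 73.2% | 25 | 68% |
| 0.10 | 7.34 | 66.9% | 21 | 61% |

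With 12 analysed per group, the large-df figures are 75.7%, 69.4% and 60.3%.

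**Step 5: rejection rate of the planned test at f = 0.25.** Simulated at 158 analysed, it stays between 78% and 80% over ICC 0.01 to 0.10. The inflated alpha offsets the lost precision.

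**The case against.** The strongest objection is that everything rests on an ICC the protocol does not give. The training lasts one and a half days plus two 180-minute boosters, outcomes are taken at 6 and 12 months, and some are physiological (hair cortisol, salivary alpha-amylase, 24-hour heart rate variability). Nothing in the document shows that these cluster by training group. With one arm nested and ICC 0.01–0.02, type I error is about 6% and power with large df is 77–79%. If nobody dropped out, a valid large-df test at 200 leaders, 10 per group, would keep 80% power up to an ICC of about 0.06. All of this stands. It makes the size uncertain and the statement conditional. It does not supply a reason to fix the ICC at exactly zero, which is what the stated model and calculation do.

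A reader might also infer more than the document supports:

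- **That the planned test has well under 80% power.** It does not. Step 5 shows that it still rejects about 80% of the time at f = 0.25. The lower figures belong to a test that holds its 5% level.
- **That reported confidence intervals will be too narrow.** The Statistical methods section plans F tests and mentions no intervals for leader outcomes. The point would apply only to an interval taken from the same model.
- **That leaders are also clustered by enterprise.** The article does not say that several leaders from one enterprise will enrol, so this is not part of the point.

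It could be said that a full analysis plan would settle the matter. But this is not an omitted detail. The article states a specific model and a specific sample size, and both assume independence.

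**Conclusion.** Wrong as written. Individual randomisation, followed by group training in one arm only, gives a partially nested design, and the named ANOVA/MANOVA and the sample size both ignore it. Unless the training-group ICC is zero, the time × group tests are anti-conservative, and alpha 0.05 and power 0.80 cannot both be met at 158 analysed.

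The size is a range because the ICC is assumed. At 0.02 / 0.05 / 0.10, type I error is about 6% / 8% / 11% and valid power about 77% / 73% / 67%, or 73% / 68% / 61% with small-group df. This supposes ten groups, 21% loss spread evenly over them, and the same ICC for both time contrasts. The ICC may differ by outcome, so the protocol does not support a claim that every leader outcome is affected to this degree.

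**What to change.** 1. Record the training group of each intervention leader, including those who drop out, as groups are formed.
2. Replace the repeated-measures ANOVA for leader outcomes by a mixed model for the three time points. Give it a random training-group effect on post-baseline change in the intervention arm only, each control leader as a singleton, and Satterthwaite-type df. Test time × group in that model.
3. In the sample-size section, state the assumed ICC range and group size, and give power at 158 analysed over that range in place of a flat 80%.

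The cost is one ID variable and revised analysis text, somewhat wider error bars, and a less favourable stated power. No extra participants are required. The change makes the power statement honest but does not restore 80%. With groups of the same size and large df, restoring it would take about 200 × DE enrolled: 214, 235 or 269 leaders at ICC 0.02, 0.05 or 0.10.

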##### Questionnaires

All subsequent questionnaires are collected at three measurement times (T_0_, T_1_, T_2_). The target outcome is the change in the intervention group compared to the waiting control group over time.

*Perceived Stress-Reactivity-Scale* [52]. The PSRS assesses perceived stress reactivity on 5 scales: reactivity to social assessment (5 items, “If I am wrongly criticized by others ...”), reactivity to failure (4 items, e.g., “If I did something wrong ...”), reactivity to social conflict (5 items, e.g., “When I argued with other people ...“), reactivity to work overload (5 items, e.g., “When I have little time for my work ...”) and prolonged reactivity (4 items, e.g., “When I have free time after strenuous work ...“). In addition, an overall score can also be calculated. All items are answered by agreeing with one of three default answers. Scale reliability is sufficiently high and varies between α = .79 and α = .82 with α = .89 for the total score (Cronbach’s Alpha).

*Effort Reward Imbalance Questionnaire (ERI,* [53]). The ERI conducts self-assessments of psychosocial workloads on three scales: exertion (6 items, e.g., “I am often interrupted and disturbed in my work”), reward (11 items, e.g., “I get the recognition I deserve from my superiors”) and over-commitment (6 items, e.g., “Those who are closest to me say I sacrifice myself too much for my job”). Reward is a multidimensional concept and consists of the following subscales: recognition, pay/progression and job security. The exertion and reward dimensions are assessed with five-point Likert-scale, ranging from “unexposed to adverse condition” (1) to “exposed to adverse conditions and very distressed” (5). Over-commitment is measured with a four-point Likert-scale, ranging from “Strongly disagree” (1) to “Strongly agree” (4). The internal consistency of the scales is sufficiently high and between α = .62 and α = .90 (Cronbach’s Alpha).

*Hospital Anxiety and Depression Scale (HADS, Herrmann, 1997).* The HADS is a 14-item questionnaire (7 items each for anxiety and depression) for self-assessment of depressive (e.g., “I still enjoy the things I used to enjoy”) and anxiety symptoms (e.g., “Worrying thoughts go through my mind”). All items are answered by agreeing with one of four default answers. Scale reliability is high with α = .86 for anxiety and α = .91 for depression (Cronbach’s Alpha).

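### The group-by-time test treats baseline as an outcome level and never adjusts for it, so precision is lost that a baseline-adjusted model would recover at no cost

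*Protocol article*

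**What the plan says.** The sample size paragraph (Method, Population and sample size, Leaders) describes a 2 × 3 mixed design with "factor 2 (point in time): baseline, 6 months and 12 months later", so baseline is a level of the repeated factor. The trial design section says the same. The size was set for a repeated-measures MANOVA with "α-error = .05" and "test strength 1-β = .80", giving 158 evaluable leaders and 200 recruited.

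The Statistical methods section plans a two-factor repeated-measures ANOVA with group as the between-person factor: "Thus, we will test the interaction effect of time x group for the different outcome variables". The core hypothesis is that stress measures "will significantly decrease from baseline to follow-up measurements for participants in the intervention group". The Questionnaires section puts the target as a comparison: "The target outcome is the change in the intervention group compared to the waiting control group over time".

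Covariates enter if a demographic variable correlates with the outcome or differs significantly between the groups. The baseline value of the outcome itself is not named as a covariate.

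**The concern.** With three time levels and two groups, the interaction has (2 − 1)(3 − 1) = 2 degrees of freedom. It is equivalent to comparing the two arms on the changes T1 − T0 and T2 − T0. Each change subtracts the whole baseline value, including its measurement noise and day-to-day variation.

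Randomisation already makes the expected T0 value equal in the two arms, so there is no baseline group difference to estimate. A regression on T0 removes only the part of the baseline that predicts follow-up. Full subtraction is efficient only when the correlation between visits is close to 1.

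At stake is precision on every leader outcome, in a trial that expects to lose 21% of its participants to drop-out and missing values.

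**Working it through.** **Inputs from the protocol article:** f = .25, alpha .05, power .80, three time points, two equal groups, 158 evaluable leaders. (The printed 59 per group does not fit 158, since 158/2 = 79; I use 158.) **Assumed, because the article gives neither:** a correlation rho between visits of .3 to .9 under compound symmetry, and three patterns of effect over time.

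**1. The plan's own figure.** For the repeated-measures MANOVA interaction, noncentrality = f² × N = .0625 × 158 = 9.875, with 2 and N − 3 = 155 df. Power is .802; N = 156 gives .797. So 158 is the smallest even N that reaches .80, and 158/(1 − .21) = 200. The stated size is reproduced.

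**2. Noncentrality of the two tests.** Let the group differences at T1 and T2 be proportional to a and b, with unit variance. Apart from a common factor:

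- planned test (changes from T0): a² + b² − (a + b)²/3
- joint 2-df test adjusted for T0: a² + b² − rho(a + b)²/(1 + 2rho)

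For rho between 0 and 1, rho/(1 + 2rho) is below 1/3, so the adjusted test never has the smaller noncentrality when a + b is not zero.

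Example, equal effects (a = b = 1) at rho = .7: planned 2 − 4/3 = .667; adjusted 2 − .7 × 4/2.4 = .833; ratio 1.25. Noncentrality rises from 9.875 to 12.34, and power from .80 to .89.

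**3. Power at N = 158, two-sided .05**, with the planned test held at 9.875 (power .80) in every row; adjusted test with 2 and 154 df:

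| Effect pattern | rho .3 | rho .5 | rho .7 | rho .9 |
|---|---|---|---|---|
| Equal at T1 and T2 | .98 | .94 | .89 | .83 |
| Half at one follow-up | .96 | .91 | .87 | .82 |
| One follow-up only | .88 | .85 | .83 | .81 |

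If the correlation instead decays with time (.5 or .7 between adjacent visits), the adjusted 2-df test has .84 to .95 over equal and half-effect patterns, again above .80 throughout.

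**4. A single contrast on the average of T1 and T2**, adjusted for T0 (1 df). Its noncentrality on the same scale is (a + b)²/[2(1 + 2rho)]:

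| Effect pattern | rho .3 | rho .5 | rho .7 | rho .9 |
|---|---|---|---|---|
| Equal at T1 and T2 | .99 | .97 | .94 | .90 |
| Half at one follow-up | .96 | .91 | .86 | .80 |
| One follow-up only | .57 | .48 | .42 | .37 |

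With equal effects it stays above .90 up to rho of about .88.

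**5. Where the gain comes from.** For equal effects, a 1-df contrast on change scores without baseline adjustment has power .88 at any rho. Part of the gain in step 4 therefore comes from assuming the shape of the effect. The gain in step 3 comes from baseline adjustment alone.

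**The case against.** The strongest reply is that nothing is stated wrongly. The interaction is a valid test of change relative to control, the trial is sized at its declared power for that test, and an omnibus test is robust to an unknown time course. All of this stands. The time course is open: boosters fall at 3 and 6 months and T1 is at 6 months, so an effect that grows or fades is plausible. The reply does not, however, defend leaving T0 out as a covariate, because the adjusted 2-df test keeps the same robustness and had more power in every pattern tried.

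A reader might infer three stronger points that the documents do not support.

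- That baseline adjustment lifts power from 80% to above 90% outright. That needs the T1/T2 average, an equal effect at both follow-ups and rho below about .88. The article fixes none of these, and the averaged contrast falls well below the planned test if the effect is at one follow-up only.
- That the planned test is defective because it also rejects for worsening. Any two-sided 1-df test does so too; direction is read from the estimates.
- That the plan yields no effect estimates. The ANOVA gives group means at each visit, Bonferroni-corrected comparisons are foreseen, and the choice of contrasts and intervals is commonly left to the analysis plan.

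**Conclusion.** The point holds as one of efficiency. The article fixes T0 as a repeated level and limits covariates to demographic variables, so baseline information that will already be collected is not used to reduce variance. Adjustment multiplies the noncentrality by between 1.02 (effect at one follow-up, rho .9) and 1.88 (equal effects, rho .3), which takes power from .80 to between .81 and .98. The gain is negligible when the correlation is high and the effect is confined to one visit, and substantial when the correlation is moderate and the effect is sustained.

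The exact figures rest on compound symmetry, complete data on 158 leaders and the design effect. The direction of the gain was the same under the decaying correlations checked. Neither the validity of the planned test nor the stated N of 158 is in question. Replacing the omnibus test by an average over follow-ups is a separate choice with a real downside, and it is not needed for the gain.

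**What to change.** For each leader outcome, analyse T1 and T2 in a longitudinal model adjusted for the T0 value of that outcome, or equivalently with the T0 means constrained equal across arms. Test the two group differences jointly and report each with a 95% confidence interval. The demographic covariate rule does not replace this adjustment.

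Make the T1/T2 average the primary contrast only if a sustained effect is declared as the target in advance, with the assumed correlation and time course stated. That would be a choice of estimand as well as of wording.

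The baseline adjustment itself costs a change of analysis text: no new data, no larger sample. If fitted as a mixed model, it also keeps the 6-month value of leaders lost before 12 months, in line with what the section on missing data and drop-outs intends.
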